## Abstract

**Background:**

Chronic tinnitus is a common incurable condition often associated with depression, anxiety, insomnia and reduced quality of life. Within National Health Service (NHS) audiology in the United Kingdom (UK), no standard protocol currently exists for the treatment of tinnitus. Counselling is only available in less than half of audiology departments, and there is no agreed standard for what constitutes tinnitus counselling. There is substantial evidence from systematic reviews for the clinical benefit of cognitive behaviour therapy (CBT) for tinnitus delivered by clinical psychologists or psychiatrists, but no studies have sufficiently evidenced the NHS model of tinnitus care where management is increasingly being delivered by audiology professionals. In a pilot randomised controlled trial (RCT), this study aims to evaluate the feasibility of comparing a psychologically informed guidance manual developed to support audiologist management of tinnitus with usual treatment.

**Methods/design:**

Phase 1 consisted of three development stages: (1) a scoping review to generate a comprehensive set of tinnitus counselling components, (2) a Delphi survey involving expert patients (*n* = 18) and clinicians (*n* = 21) to establish consensus on the essential core attributes of tinnitus counselling, and (3) incorporation of these elements into a manualised care protocol. In phase 2, following training in a dedicated workshop, the manualised intervention will be delivered by three experienced audiologists across three different sites. Patients (*n* = 30) will be randomly allocated to receive either (1) psychologically informed management from an audiologist trained to deliver the manualised intervention or (2) treatment as usual (TAU) from an audiologist who has not received this training. Quantitative outcome measures will be administered at baseline, discharge and 6-month follow-up. Qualitative interviews with participating patients and clinicians will be conducted to gather perspectives on the feasibility and acceptability of the manualised intervention.

**Discussion:**

The feasibility of proceeding to a definitive RCT will be assessed via compliance with the manual, willingness to be randomised, number of eligible participants, rate of recruitment, retention and collection of quantitative outcome measures. This research offers an important first step to an evidence-based, standardised and accessible approach to tinnitus care.

**Trial registration:**

ISRCTN13059163. Date of registration: 6 May 2016

## Background

Chronic tinnitus is a common incurable condition where sound is perceived in the absence of acoustic stimulation. It affects about 10% of people in the United Kingdom (UK) [1] and is often associated with insomnia and hearing difficulty [2] and psychological problems such as depression and anxiety [3]. Within National Health Service (NHS) audiology, tinnitus is treated using a number of recommended interventions [4], but no standard protocol exists. As such, practices vary; sound therapy and patient education are widely available, but psychological interventions are only available in less than half of audiology departments [5].

A recent model of tinnitus posits that negative automatic thoughts and safety behaviours maintain tinnitus-related distress and that psychological interventions should be directed at reducing or removing these [6]. The benefit of cognitive behaviour therapy (CBT) delivered by clinical psychologists or psychiatrists is recognised [7–9], but there is no evidence for the effects of psychological interventions when delivered by audiologists [9]. Now that specialist tinnitus care is increasingly becoming the domain of audiologists due to the attrition of hearing therapists and the dearth of clinical psychologists in the UK, their delivery of a psychologically informed treatment represents a potentially cost-effective and highly accessible route to improving tinnitus patient care within the NHS. In their review of psychological interventions amongst tinnitus suffers, Wan Suhailah and colleagues [10] concluded that, due to the shortage of clinical psychologists, a simplified version of psychological intervention implementable by other clinicians should be developed to treat tinnitus. The Department of Health [4] also posit that audiologists should be able to provide psychological therapies where required. Furthermore, the effectiveness of audiologist-delivered CBT was one of the top 10 priority questions identified by clinicians and patients in the recent James Lind Alliance Tinnitus Priority Setting Partnership [11]. However, specialist audiological counselling skills are not a core requirement of the current audiologist training pathway in the UK, and in a survey, only 15% of audiologists in England considered themselves specialists in tinnitus care provision [5]. Although there is an appetite amongst audiologists to undertake further training in psychological therapies, the training is not standardised [12], nor has it undergone any formal evaluation. Thus, many audiologists have concerns about what degree of training is appropriate in order to formally ‘counsel’ [13]. This study represents a first step towards providing an evidence-base to support inclusion of psychological support for tinnitus into routine audiologist practice. In accordance with Medical Research Council (MRC) recommendations for developing and evaluating complex interventions [14], a phased approach to this study has been adopted, incorporating a development phase and an intervention phase.

The specific aims are:To develop a treatment manual for a trained audiologist to use when providing psychological support for people with tinnitusTo conduct a feasibility trial to establish whether this manualised tinnitus treatment including core counselling elements versus treatment as usual (TAU) can be evaluated at the level of a large scale RCTTo conduct qualitative interviews with participating patients and audiologists to gather perspectives on the feasibility and acceptability of the manualised intervention

## Method

### Phase 1: development phase

This phase consisted of three stages:
*Scoping review:* components of psychological therapies for tinnitus were identified via a comprehensive scoping review of trials registers and academic databases of published literature, and editorials, conference abstracts and dissertations in the grey literature. A set of psychological therapy components were generated that underwent thematic analysis and were grouped across 25 themes [15].
*Delphi survey:* the set of psychological therapy components formed the basis of an online 3-round Delphi survey ([name] et al., in preparation). The Delphi process is commonly used to develop consensus amongst experts when defining new interventions in health service research [16] and has been recognised as an appropriate method for this purpose [17]. The survey panel comprised patients (*n* = 18) who had experienced tinnitus counselling or psychological therapy and clinicians (*n* = 21) who had delivered counselling or psychological therapy for people with tinnitus, to establish consensus on the components of psychological therapy that audiologists could and should deliver in tinnitus management. Novel components elicited from the open-ended question in the first round were added to those generated from the scoping review. These 160 components were then rated in two subsequent rounds, where individual panellists were invited to reconsider their initial decisions in the light of overall levels of agreement across panellists. Consensus for inclusion or exclusion was taken as 80% or more of all panellists rating the component at points 6–7 or 1–2 on the scale, respectively. Consensus on the importance and relevance of 76 components was reached. For the remaining 84 components, consensus was not reached.
*Manualised protocol:* this stage comprised manualising the core components identified in the Delphi survey for testing in a feasibility trial as a specialised psychologically informed intervention delivered by audiologists. In order to describe and standardise the intervention, this stage commenced with a full day reference group meeting involving steering group and study team members to decide on which components to include and how to incorporate them into a psychologically informed manualised care protocol. It was agreed in this meeting that a working framework for the manual would comprise the following sections: rationale, assessment, education, treatment planning/goal setting, management/self-management and relapse prevention. All 76 components for which consensus for inclusion was reached were first considered for allocation under these headings. This was followed by considering whether any of the 84 components for which consensus was not reached should be included and if so, under which headings they would be written into the manual. Decisions were based on level of agreement from the Delphi survey, whether components had a good evidence-base, theoretical cohesiveness and what could realistically be included in a short, low intensity intervention delivered by audiologists, on the basis of resource limitations and time-limited training. Individual members of the team (including patient representatives, audiologist, hearing therapist, cognitive behaviour therapist and researchers) worked to develop specific sections of the manual in accordance with their areas of expertise and taking note of research into what makes a good treatment manual [18]. Finally, the manual was reviewed and amended to reflect a ‘whole’ in terms of style, coherence and theory.

### Phase 2: intervention phase

#### Feasibility trial design

The design is a non-blinded, multicentre, randomised controlled feasibility trial of psychologically informed treatment from an audiologist who has received training in the use of the manual, versus TAU from an audiologist who has not, for people with tinnitus (Fig. 1).

**Fig. 1 Fig1:**
[figure not shown]
Psychologically informed treatment for tinnitus participant flow chart

#### Participants

Thirty participants referred by a general practitioner (GP) or an ear, nose and throat (ENT) specialist for tinnitus management will be recruited. Recruitment will be across three NHS audiology departments which provide tinnitus services in Nottingham University Hospitals NHS Trust, Derby Teaching Hospitals NHS Foundation Trust and Sherwood Forest Hospitals NHS Foundation Trust. GP referral sample size was calculated to estimate critical parameters such as recruitment rate and acceptability of randomisation and different outcome measures. Following consultation with six clinical sites, it was estimated that, in general, recruitment of two participants per month per site was readily achievable. The sample size was therefore predicted rather than actual as it was determined by forecast, the number of sites and the timeframe of the project. It is not necessarily limited to the inclusion of just two participants per site per month. A predicted recruitment rate does however test the feasibility and likely timeframe of conducting a fully powered, multi-centre RCT. Furthermore, in order to estimate standard deviation, which can be used as part of a sample size calculation for an explanatory RCT, two authoritative papers taken together put the recommended estimated feasibility trial sample size in between 24 and 50 [19, 20].

##### Inclusion criteria

For inclusion in the feasibility trial, patients must reflect the typical population that might be expected to take part in a phase 2 clinical trial. The typical population includes adults aged 18 and over, comprises more males than females, shows a trend towards increasing age to a peak of between 60 and 69 years [21] and a bias towards people of higher deprivation/level of education [22]. The sample is also likely to contain a proportion of people who suffer from comorbid mental health conditions, e.g. anxiety and depression, and medical conditions, e.g. hypertension and diabetes mellitus [21]. The majority are also likely to have some degree of hearing loss [22]. Participants will be required to demonstrate the intellectual/cognitive capacity to provide informed consent and have sufficient mobility to attend clinics. No exclusions will be made on the basis of previous experience with psychological services. All patients will be enrolled at or before their first visit to audiology and have a primary complaint of tinnitus. Patients will also be required to present with a clinically relevant need, determined by a questionnaire score of >24 on the Tinnitus Functional Index (TFI) [23] indicating that tinnitus is at least a moderate problem. Offering this intervention to patients without such a clinically relevant need may be considered unnecessary treatment. All participants must be willing to complete questionnaires and to take part in follow-up semi-structured interviews about their experiences of taking part in the study.

##### Exclusion criteria

For the feasibility trial patients whose symptom of tinnitus is actually of a medically treatable origin (i.e. not chronic subjective tinnitus, but objective tinnitus for instance, where the noise can be detected by a third party) will be excluded. Also excluded will be patients who are unable to communicate in English and those participating in other research in tinnitus management at any time from consenting to their participation. Finally, patients who have comorbid conditions (e.g. psychotic disorders or dementia) which render them unable to give informed consent will be excluded. No exclusions will be made specifically on the basis of any medications patients may be taking.

### Ethical considerations

Ethical approval was granted by North West – Preston Research Ethics Committee (reference 16/NM/0047). Informed consent will be sought from participants in accordance with Good Clinical Practice (GCP) after thorough information about the study is provided by the researcher or site principal investigator (PI). The PI at each site will have responsibility for reporting of adverse events (AEs) to the chief investigator (CI) who will then inform the Research and Innovation Manager and Trust Governance Manager as required. Local policies and procedures at the three sites will be followed for reporting and investigating such incidents.

### Randomisation

Participants will be 1:1 randomised using the randomisation function in Microsoft Excel. First participants will be assigned a number between 1 and 10 for each of the three sites, according to chronological order of recruitment. For each site, these numbers will be given another random number using the Excel randomisation function and the participants 1 to 10 for each site will be ordered according to their associated randomly generated number. Those with the greatest five random numbers per site will be allocated to TAU. This process will be completed by telephoning a member of the research unit not involved in the trial after the participant has been screened as eligible and provided informed consent.

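### Allocation by one disclosed block of ten per site lets the last allocations be deduced in an open trial, leaves no slot for an eleventh patient at a site, and can leave the arms uneven if a site falls short

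*Protocol article*

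**What the plan says.** The Randomisation section of the Protocol article sets out the method: "Participants will be 1:1 randomised using the randomisation function in Microsoft Excel". It continues: "First participants will be assigned a number between 1 and 10 for each of the three sites, according to chronological order of recruitment". Each number then receives an Excel random number, "the participants 1 to 10 for each site will be ordered according to their associated randomly generated number", and "Those with the greatest five random numbers per site will be allocated to TAU". On release it says: "This process will be completed by telephoning a member of the research unit not involved in the trial after the participant has been screened". The call thus follows both the eligibility check and consent.

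The Participants section gives the target ("Thirty participants referred by a general practitioner (GP) or an ear, nose and throat (ENT) specialist for tinnitus management will be recruited") and the sites ("Recruitment will be across three NHS audiology departments which provide tinnitus services"). Of the forecast of two recruits per site per month it says: "It is not necessarily limited to the inclusion of just two participants per site per month".

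Three other statements bear on the point. The Feasibility trial design section calls the trial non-blinded, with the arms treated by trained and untrained audiologists respectively. The Outcome measures section accepts 20 of 30 recruits as success. The Statistical analysis section plans no hypothesis test.

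**The concern.** The scheme is one permuted block of ten at each site, with its length and split published. Three consequences follow.

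- **Deducible allocations.** Once one arm has used its five places at a site, every remaining allocation there is known. Staff see which audiologist treats each patient, so past allocations are easy to count. Under Ethical considerations, consent information may come from the researcher or the site principal investigator, so a person approaching patients may know the next arm. That could influence who is enrolled, and through that the descriptive comparisons and the figures on willingness to be randomised.
- **No eleventh slot.** The total of 30 is reached only if all three sites reach exactly ten.
- **Incomplete blocks.** Balance is guaranteed only when a block is full. The plan accepts a total of 20, at which at least one site's block is unfinished or unused.

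**Working it through.** **Inputs.** From Randomisation: 10 places per site, 5 TAU. From Participants: 3 sites, target 30, forecast of 2 per site per month. From Outcome measures: success at 20. Assumed, because the article does not give them: Poisson recruitment, the length of the recruitment window, and the split across sites at 20 recruits.

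**The plan's own figures.** 3 × 10 = 30 and 3 × 5 = 15 TAU, so full recruitment gives exactly 15:15. Also 0.65 × 30 = 19.5, rounded up to 20. Both reproduce.

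**Certain allocations.** C(10,5) = 252 equally likely sequences per site. The number of final allocations that are certain is 1, 2, 3, 4 or 5 in 140, 70, 30, 10 and 2 sequences.
- Mean = (140 + 140 + 90 + 40 + 10)/252 = 420/252 = 1.67 per site, or 5 of 30.
- At least two certain: 112/252 = 44.4%. At least three: 42/252 = 16.7%.
- Only the tenth is certain in every sequence.

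**Best-guess accuracy.** Always guess the arm with more places left. Expected correct = 5 + (2^10/252 − 1)/2 = 5 + (4.063 − 1)/2 = 6.53 of 10, against 5 by chance.

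**Effect of the cap on recruitment.** Each site recruits Poisson(2t) in t months. With the cap, P(reach 30) = P(Poisson(2t) ≥ 10)³. Without it, P(reach 30) = P(Poisson(6t) ≥ 30). At t = 5 these are 0.542³ = 0.159 and 0.524.

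| Months (assumed) | Reach 30, capped | Reach 30, uncapped |
|---|---|---|
| 5 | 16% | 52% |
| 6 | 43% | 86% |
| 7 | 71% | 98% |

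Five months is simply 30/(3 × 2). For the 20-recruit criterion at five months, convolving three site counts each truncated at ten gives 97.3%, against P(Poisson(30) ≥ 20) = 97.8%.

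**Imbalance at 20 recruits.** With m patients at a site, P(k TAU) = C(5,k)C(5,m−k)/C(10,m), convolved over the sites.

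| Assumed split | P(12:8 or worse) | P(13:7 or worse) |
|---|---|---|
| 7/7/6 | 26.1% | 5.8% |
| 8/6/6 | 25.3% | 5.4% |
| 10/5/5 | 19.1% | 2.8% |
| 10/7/3 | 15.3% | 1.4% |
| 10/10/0 | 0% | 0% |

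**What varying blocks would change.** These results cover the first ten allocations per site, with block sizes equally likely and an observer who knows the possible sizes but not their order.
- Blocks of 4, 6 and 8: about 0.24 certain allocations per site by exact enumeration (about 0.26 by simulation), against 1.67. Best-guess accuracy is about 66%, against 65%.
- Smaller blocks are easier to guess: about 68% for 4/6 and 71% for 2/4.
- P(12:8 or worse) at 7/7/6 falls from 26% to about 9% with 4/6/8, or about 7% with 4/6.
- At a full 10/10/10, a difference of four or more between the arms has probability about 12% with 4/6/8. It is zero under the present rule.

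**The case against.** The strongest reply is that little depends on this. An independent person releases each allocation only after eligibility and consent. No hypothesis is tested, so selective enrolment would mainly distort between-arm comparisons that are not the purpose here. Ten per site matches the target exactly and gives each site five patients on the manual, which is a defensible aim when clinician compliance and clinician interviews are outcomes. All of this stands and limits the weight of the point. Telephone release hides the list, however. It does not stop staff counting to five.

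A reader might infer more than the documents support:

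- *That the cap contradicts the Participants section.* It does not. That sentence frees the monthly pace, not the site total, and ten per site at any speed is compatible with it.
- *That the cap spoils the recruitment estimate or the go/no-go decision.* A site that fills early still yields its monthly rate and its share of eligible patients. The chance of meeting the 20-recruit criterion moves by about half a percentage point.
- *That early stopping is planned.* It is not. Imbalance would come only from under-recruitment.
- *That the procedure is unworkable because ten numbers cannot be ranked call by call.* It works if the list is drawn beforehand. The section does not say so, but a condensed article may leave that to the full protocol.
- *That shorter blocks make allocation harder to guess overall.* They do not, as the figures above show.

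**Conclusion.** The point holds at modest weight. One disclosed block of ten per site in an open trial makes the tenth allocation at each site certain to anyone who has tracked the earlier ones, with 5 of 30 certain on average. This part needs no assumption beyond the written rule and staff who keep count.

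The missing eleventh slot lowers the chance of reaching 30 appreciably under the assumed Poisson model. The size depends on the window, which the article does not state, and the success criterion of 20 is nearly untouched. Imbalance at 20 recruits is possible rather than likely: from zero to about 26% for a 12:8 or worse split, depending on the assumed site split.

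This is a cheap improvement worth making. It does not invalidate the trial.

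**What to change.** Before the first recruit, have the off-trial research unit generate a list for each site that is longer than ten, in randomly varying blocks (for example 4, 6 and 8), and freeze it as fixed values. Do not disclose the block sizes to sites. Release one allocation per telephone call, and stop at 30 in total, so that a site may pass ten. Avoid very small blocks, which raise guessing accuracy. The gain depends on keeping the sizes undisclosed: a known block of 2m still leaves 2m/(m + 1) certain allocations on average, which is 10/6 = 1.67 for ten and 4/3 = 1.33 for four.

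The work is list generation and a change of protocol wording. The price is that the final arms may differ by a few patients instead of being exactly 15:15, and that sites and their trained audiologists may see unequal numbers. If similar experience of the manual at each site matters, keep a soft site maximum somewhat above ten.

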### Interventions

Psychologically informed treatment plus TAU: the intended purpose of the manual is to provide audiologists with a resource to support their work with people who have tinnitus in a psychologically informed therapeutic alliance to identify individual needs, set joint goals, reach shared and informed decisions and promote patient self-management. It is designed to go beyond the directive education and advice that might be considered TAU. Based on estimates from current practice, patients will participate in approximately five sessions, each lasting 1 h on average, delivered by an audiologist who attended a two-day training workshop on the manual.

The manual is divided into nine sections (Table 1). Section 1 provides the background and overview of the manual, including the processes and skills for developing a relationship with the patient. Section 2 involves assessment through a standardised interview, where the aim is for individual patient needs to be identified and a therapeutic alliance to begin. The rationale for psychologically informed treatment will then be discussed (section 3) prior to collaborative goal setting and treatment planning (section 4). Based on individual need, the audiologist and patient will work on relevant areas of tinnitus education (section 5) and management/self-management strategies (section 6). These include managing the emotional consequences of tinnitus, rapid relaxation, managing fear and avoidance behaviours, changing unhelpful thoughts and beliefs, promoting physical exercise, promoting good sleeping habits, attention, monitoring and acceptance, and sound therapy (enrichment). The treatment concludes with a focus on relapse prevention (section 7). Section 8 is a bibliography containing references related to the intervention and further reading for the audiologist or patient. The appendices (section 9) contain materials used for training in the manual. Audiologists will be guided on appropriate treatment areas to cover and resources to use from an accompanying ‘toolkit’ (Table 2). They will receive periodic peer supervision and from the manual trainers.

**Table 1 Tab1:** Psychologically informed treatment for tinnitus manual contents

1. Introduction	
1.1.Background	
1.2.Overview of manual	
2. Patient assessment	
3. Rationale for psychologically informed treatment	
4. Goal setting/treatment planning	
5. Patient education	
6. Patient management/self-management	
6.1.Managing the emotional consequences of tinnitus	
6.2.Rapid relaxation	
6.3.Managing fear and avoidance behaviours	
6.4.Changing unhelpful (negative) thoughts and beliefs	
6.5.Promoting physical exercise	
6.6.Promoting good sleeping habits	
6.7.Attention, monitoring and acceptance	
6.8.Sound therapy (enrichment)	
7. Relapse prevention	
8. Bibliography	
9. Appendices	
A1.Communication in rehabilitation	
A2.The relational skills model—setting up the relationship	
A3.The relational skills model—developing the relationship	
A4.The relational skills model—working with the relationship	
A5.The relational skills model—the established relationship	
A6.Providing explanations	
A7.Teach-back technique

**Table 2 Tab2:** Psychologically informed treatment for tinnitus toolkit

T1 Tinnitus functional index (and scoring rubric)	
T2 Tinnitus case history questionnaire	
T3 Formulation worksheet (for sections 2 and 6.3)	
T4 BTA leaflet all about tinnitus ver.1.4	
T5 Cognitive model of tinnitus psychology tool	
T6 Stages of change model	
T7 Goal setting sheet	
T8 Action planning sheet	
T9 Goal setting and action planning practice framework	
T10 What keeps tinnitus going psychology tool	
T11 What causes tinnitus psychology tool	
T12 Meaning in tinnitus psychology tool	
T13 BTA leaflet tinnitus and stress ver.1.4	
T14 Relaxation training diary	
T15 Fear and avoidance example formulation	
T16 Exposure worksheet	
T17 Negative thinking example formulation	
T18 Unhelpful thinking styles sheet	
T19 Thought record—blank copy	
T20 Thought record—example copy	
T21 Physical exercise example formulation	
T22 Physical exercise diary	
T23 Sleep cycles sheet	
T24 Sleep diary	
T25 BTA leaflet taming tinnitus ver.1.3	
T26 Acceptance in metaphors sheet	
T27 Mindfulness: three simple ways to get present sheet	
T28 My ‘managing tinnitus’ blueprint: making a plan for well-being	

Treatment as usual (TAU): patients will be assessed and managed by an audiologist who has not received training in psychological therapy and has not received training in the psychologically informed treatment for tinnitus. Based on routine clinical practice, this is likely to include management of tinnitus education and advice over approximately three sessions, each lasting 1 h on average.

